### **8.3 Economic evaluation**

The aim of the economic evaluation is to compare the costs and health effects of a lifestyle program versus “usual care”. The analysis will be a cost-effectiveness analysis with the proportion of healthy singleton of more than 37 week gestation born after vaginal delivery as the primary outcome.

The economic evaluation will be performed from a societal perspective. Direct medical and non-medical costs (intervention costs, time and travel costs) as well as indirect non-medical costs (productivity losses) will be taken into account.

We will build on the work of the ZonMW funded “Paraplu” study, in which cost data of six cost-effectiveness studies were integrated. Dr [name] played an important role in this process.

The time horizon will be from randomisation to the end of follow-up. Resource use will be recorded as individual patient data in the CRF. In addition each woman will receive a questionnaire for details on associated direct costs of professional care and on indirect costs like transportation, sporting activity and productivity loss. These questionnaires will be handed out in consultation 2, week 3 of the lifestyle module or at the start of fertility treatment for women that were randomised for “usual care”. This will be repeated at the time points of the other questionnaires (12, 24 and 52 weeks after randomisation and at the end of follow-up).

Resource use will be valued according to Dutch guidelines. Intervention costs will be determined based on actual resource use obtained from the centers. Costs will reflect the following

resources: staff, materials, equipment, housing, overhead. Productivity loss will be valued by the friction cost method according to Dutch guidelines (Oostenbrink et al. 2004). Outcome of pregnancy will be recorded and valued using tariffs or data from the literature (Lukassen et al, 2004).

Detailed information on maternal complication will be obtained from obstetricians treating the woman concerned using patient medical files. Six weeks after the expected day of delivery all women will be contacted by telephone to ask information on the delivery and on the health of the child. If the child has been hospitalised the paediatrician treating the child will be contacted for further information.

Scenario analysis will be performed to model cost-effectiveness beyond the time horizon of the study. For longer term analyses, costs and effects will be discounted at commonly accepted rates. Sensitivity analysis will be performed on costs, pregnancy rates of the two groups and the valuation of different outcomes (no child, handicapped child, twin, healthy child, obstetric complications). Uncertainty surrounding cost-effectiveness estimates will be explored by bootstrapping. Cost will be presented in euros.

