### **5. TREATMENT OF SUBJECTS**

#### **5.1 Investigational treatment**

**THE “USUAL CARE” ARM:** In the “usual care” arm treatment will be started if the individual prognosis, based on the Hunault model (Hunault et al.2004) is less than 30% chance of conception within one year or when more than 3 years subfertility (guideline NVOG) justifies starting treatment. Even so, in case of chronic anovulation, ovulation induction will be started. Fertility treatment can either be IUI, IVF or ICSI whatever is indicated according to the Dutch guideline on IVF treatment (NVOG). In anovulatory patients, ovulation induction will be started using clomiphene, or gonadotrofines, which is applicable. When the Hunault model shows a prognosis of more than 30% pregnancy chance in the forthcoming year (and patients are less than three years subfertile), expectant management will be offered.

**THE EXPERIMENTAL ARM:** The overweight intervention is based on the lifestyle module which is developed in ZONMW project (50-50110-98-078) and will be adapted for the study

proposal in this specific group of subfertile woman for a duration of six months. The software module developed, used and evaluated in this program will be adapted for this subfertile patient group. The use of the software program will reduce practice variation between fertility centres. The lifestyle intervention is based on the recommendations of Dutch CBO guideline "Diagnostiek en behandeling van obesitas bij volwassenen en kinderen" and consists of a structured lifestyle program targeted at:

1. Changing the dietary pattern.
2. Stimulating physical activity of moderate intensity.
3. Changing existing behaviour.
4. Self- monitoring.
5. Involvement of the partner.
6. Referral to psychologist when indicated.

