**FOLLOW-UP:**

All participating couples (usual care arm and the experimental care arm) will complete several questionnaires, i.e. the SF-36: measuring satisfaction, the SQUASH list: for physical activity, the FFQ: food frequency questionnaire for assessing nutrient intake): a structured questionnaire about food pattern (e.g. breakfast yes/no) and important food components (e.g. snacks, fruits and vegetables and meat), the Dutch Eating Behaviour Questionnaire (DEBQ): for assessment of restrained, emotional and external eating behaviour (van Strien 1986). Finally, several questions are completed i.t.o. history of body weight, e.g. the duration of overweight, weight fluctuations.

Questionnaires are webbased. In case a patient does not use the computer paper questionnaires will be used. Questionnaires will be completed at start, 12 weeks, 24 weeks and 52 weeks after randomisation. In addition each woman will receive a questionnaire for details on associated direct costs of professional care and on indirect costs like transportation, sporting activity and productivity loss. These questionnaires will be handed out in consultation 1, week 1 of the lifestyle module or at the start of fertility treatment for

women that were randomised for “usual care”. This will be repeated at the time points of the other questionnaires (12, 24 and 52 weeks after randomisation and at the end of follow-up).

Finally, patients who get pregnant during the period up to 24 months after randomisation will receive a questionnaire in which they can register their (self-reported) weight-gain during pregnancy. To assess gestational diabetes, an oral glucose tolerance test is advised at 28-30 weeks of gestation. Cord blood will be taken from approximately 150 patients after childbirth to assess the epigenetic and metabolic profile. The data will also be used in the follow-up study in case women give informed consent to participate in the follow up study of her child: “the preconception weight loss; does it affect infant health study” (METc: 2011/134), (the so-called “Lifestyle-kids” study).

Moreover, we will register reproductive outcome, fertility treatments as well as the course and outcome of subsequent pregnancies, including obstetrical interventions for a period up to 24 months after randomisation.

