### **WEEK 1: BASELINE EVALUATION.**

Consultation 1.

Counselling session 45-60 minutes.

Motivational counselling will include an extensive history of weight changes, knowledge and insight of weight related health problems.

Awareness, actual behaviour and lifestyle leading to overweight and history of body weight and slimming are discussed.

Counselling negative effect of overweight on frequencies of spontaneous and treatment dependent pregnancy chances and increase frequency of complications during pregnancy for mother and foetus.

The stages of change can be identified using the PACE score in the GOAL software.

DEBQ is evaluated to assess the type of eating behaviour.

Counselling and providing knowledge and advice about healthy lifestyle.

Evaluating diet questionnaire

Evaluating SQUASH score for physical activity

Healthy diet is advised aiming for a reduction of 600 Kcal/day ("Energy reduced diet"). Diet should be based on the Dutch guideline "Gezonde Voeding". Food intake should not be reduced below 1200 Kcal/day in order to achieve a sustainable lifestyle change.

Use of stepcounter is explained: 10.000 steps/day and two to three times a week sporting of at least 30 minutes of moderate intensity (60-85% of maximum heart frequency).

A questionnaire for details on indirect costs like transportation, sporting activity and productivity loss will be handed out.

Partner is involved in the counselling session

Referral to a dietician or psychologist is done in a standardized way, when appropriate.

Measuring waist circumference and weight.

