**Table 1: time schedule lifestyle intervention**

| Week | Consultation
Outpatient/
Telephone or mail | Counseling subject lifestyle program                                                                                | Duration
minutes |
|-------------|-----------------------------------------------------------|----------------------------------------------------------------------------------------------------------------------------|-----------------------------|
|             | Randomisation                                             | Baseline assessment and explanation lifestyle program; handout of "eetmeter", stepcounter and diary . Blood sample (10 cc) | 30                          |
| 1           | Outpatient 1                                              | Setting targets and planning goals; evaluating baseline measures , hand out of cost-questionnaires                         | 45-60                       |
| 3           | Outpatient 2                                              | Evaluating targets;                                                                                                        | 45-60                       |
| 5           | Telephone 1                                               | Evaluating targets                                                                                                         | 15                          |
| 7           | Outpatient 3                                              | Evaluating targets                                                                                                         | 30                          |
| 9           | Telephone or mail 2                                       | Evaluating targets                                                                                                         | 15                          |
| 12          | Outpatient 4                                              | Evaluating targets, handout of questionnaires
Blood sample (10 cc)                                                      | 30                          |
| 15          | Telephone or mail 3                                       | Evaluating targets                                                                                                         | 15                          |

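### The first cost questionnaire is tied to a programme visit in the lifestyle arm but to the start of fertility treatment in usual care, so questionnaire-based costs may be captured differently by arm, mainly before week 12

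*Supplement*

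**What the plan says.** All references are to protocol version 5 unless the SAP is named.

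- **Horizon.** Section 8.3 takes a societal perspective and counts costs from randomisation until follow-up closes, which is 24 months.
- **First form, lifestyle arm.** Section 8.3 has it "handed out in consultation 2, week 3 of the lifestyle module or at the start of fertility treatment for women that were randomised" to usual care. The follow-up text of section 5.1 has it "handed out in consultation 1, week 1 of the lifestyle module". The week 1 entry in section 6.3 agrees with week 1: "A questionnaire for details on indirect costs like transportation, sporting activity and productivity loss will be handed out". So does Table 1, which puts "hand out of cost-questionnaires" at the first outpatient visit.
- **First form, usual care.** Both section 5.1 and section 8.3 give it "at the start of fertility treatment for women that were randomised for" usual care. No calendar time is attached.
- **When usual-care treatment starts.** Under section 5.1, women with a one-year prognosis above 30% and less than three years of subfertility are not treated at once; for them "expectant management will be offered".
- **Later forms.** Sections 5.1 and 8.3 repeat the form at weeks 12, 24 and 52 after randomisation and when follow-up ends, with no difference by arm stated. No recall period is given for any form.
- **Other cost sources.** Section 8.3 also takes resource use from the CRF, programme costs from the centres' actual use, and maternal complications from medical files.
- **SAP.** It names costs in sections 5.1.1 and 5.1.3 but does not describe how they are collected or analysed.

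**The concern.** A comparison of costs between randomised arms needs the same instrument over the same period in both. Here the first form follows a fixed visit in one arm and a clinical event in the other. That event depends on prognosis and on what happens after randomisation: a usual-care woman managed expectantly, or one who conceives before treatment, may reach it late or not at all.

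The questionnaire is the only instrument named for travel, sport and lost productivity, and it also collects self-reported professional care. All of these belong in a societal cost comparison. Cost per additional healthy singleton birth is a stated aim in protocol section 2 and SAP section 5.1.1, so a measurement difference in the first weeks enters a headline result. Bootstrapping, which section 8.3 plans, describes sampling uncertainty and does not address a difference in how costs are measured. The clinical primary endpoint is not touched.

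**Working it through.** The plan gives no figure to reproduce. The check sets the passages side by side and then does simple week arithmetic.

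**Step 1: timing of the first form**

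| Source | Lifestyle arm | Usual care |
|---|---|---|
| Section 5.1, follow-up | Week 1 | Start of fertility treatment |
| Section 6.3, week 1 entry | Week 1 | Not stated |
| Table 1 | Week 1 | Not stated |
| Section 8.3 | Week 3 | Start of fertility treatment |

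Two things follow. The arm-specific anchor appears twice, so it is a stated rule and not a slip in one place. The lifestyle-arm week is contradictory within the same version and has to be reconciled.

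**Step 2: lag between arms**

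Inputs: lifestyle first form at week 1 or 3; first common form at week 12; horizon 24 months, taken as 2 × 52 = 104 weeks.

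Assumptions: programme weeks are counted from randomisation, and the week-12 form goes to every woman whether or not treatment has started. An untreated usual-care woman then has her first form at week 12.

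Lag = first form in usual care − first form in lifestyle arm:

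- Lifestyle form at week 1: 12 − 1 = 11 weeks; 11/104 = 10.6% of the horizon.
- Lifestyle form at week 3: 12 − 3 = 9 weeks; 9/104 = 8.7% of the horizon.

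These are maxima. A usual-care woman treated at once could have her form at about week 0, which is 1 to 3 weeks *before* the lifestyle arm. The lag therefore differs between women and can take either sign.

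**Step 3: if the assumption on week 12 fails**

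The later forms are described as repeats. If repeats go only to women who have had a first form, an expectantly managed woman may have no questionnaire costs at all, and the lag has no upper bound within follow-up.

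**Step 4: what the lag does to the data**

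This turns on the recall period. If the week-12 form asks about everything since randomisation, most of the gap closes, at the price of longer recall in usual care. If it asks about a shorter period, early usual-care costs are unrecorded. The documents do not say which applies.

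**The case against.** Several points on the other side have force.

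- **Only one instrument is affected.** A reader might infer that cost capture as a whole starts at different times. The documents do not support that. CRF resource use, centre-based programme costs and medical-file data do not depend on this hand-out, and section 5.1 registers fertility treatments and pregnancies in both arms over 24 months. This stands and limits the point to questionnaire-based costs.
- **The later forms are most naturally common to both arms.** Both sections speak of each woman receiving the form and align the repeats with the other questionnaires, which section 5.1 gives to both arms. This stands as the likelier reading, and it confines the gap mainly to the first 12 weeks. It does not supply a recall period.
- **The early window may be truly empty.** The protocol Summary describes the form as covering costs caused by the programme and by fertility treatment. On that description an untreated woman has little to report, and a blank would be close to a true zero. This is a fair reading, but sections 5.1 and 8.3 describe the form's content without that restriction, so it cannot be relied on.
- **No direction of bias follows.** A reader might infer that the rule biases the cost difference against the lifestyle programme, or that usual-care women with an early form are a selected, costlier group. Neither can be derived: the recall period is unstated, the share of untreated women is not given, the lag can take either sign, and the later forms are not restricted to treated women.

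**Conclusion.** The point holds for questionnaire-based costs. The current protocol states a rule that times the first cost form differently by arm and, in usual care, makes it depend on an event after randomisation, although the horizon starts at randomisation. The lifestyle-arm timing also contradicts itself (week 1 against week 3).

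For a usual-care woman not yet treated, the first form can lag by up to about 9 to 11 of 104 weeks. That rests on the week-12 form reaching every woman and on programme weeks counting from randomisation. If the week-12 form does not reach untreated women, the lag is longer. How many women are exposed, and the direction and size of any effect on the cost difference, cannot be derived from the documents. It is a bounded fault in one part of the cost comparison, and inexpensive to repair.

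**What to change.** **Protocol text.** Reconcile section 5.1, section 6.3, Table 1 and section 8.3 to one rule: cost questionnaires are anchored to randomisation in both arms, and the forms at weeks 12, 24 and 52 and at the end of follow-up go to every woman whether or not treatment has started. State the period each form covers.

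**Women already enrolled.** The amendment list shows that all 577 women were included before version 5 was approved, so a new form at randomisation would reach nobody. Follow-up was still running and SAP section 6.3 places the analysis after database lock, so an analysis rule can still be set:

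1. Compare questionnaire costs over the same windows since randomisation in both arms.
2. Do not simply drop the lifestyle arm's first form. If the week-12 form covers only the time since that form, dropping it removes early costs from the lifestyle arm alone.
3. Where the period before week 12 is not covered for a usual-care woman, treat those costs as missing and not as zero.
4. Add a sensitivity analysis restricted to the windows covered by the forms common to both arms.

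**Cost.** A few lines of wording, a little extra analysis, and some recall or imputation uncertainty for the first 12 weeks. No new visits are needed.

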## **9. ETHICAL CONSIDERATIONS**

### **9.1 Regulation statement**

The study will be conducted according to the principles of the Declaration of Helsinki (Adopted by the 18th WMA General Assembly, Helsinki, Finland, June 1964, and amended by the:

29th WMA General Assembly, Tokyo, Japan, October 1975

35th WMA General Assembly, Venice, Italy, October 1983

41st WMA General Assembly, Hong Kong, September 1989

48th WMA General Assembly, Somerset West, Republic of South Africa, October 1996

and the 52nd WMA General Assembly, Edinburgh, Scotland, October 2000

Note of Clarification on Paragraph 29 added by the WMA General Assembly, Washington 2002

Note of Clarification on Paragraph 30 added by the WMA General Assembly, Tokyo 2004 and in accordance with the Medical Research Involving Human Subjects Act (WMO)

### **9.2 Recruitment and consent**

Women eligible for the study will be referred to a research nurse by their treating doctors. This person is dedicated to counselling eligible patients, randomisation and follow-up for data, but not to the experimental intervention. We will collaborate with the research nurses who are involved in the obstetric and urogynaecological consortium. In this consortium, eight large randomised clinical trials are performed. Information on this infrastructure is obtainable from <http://www.studies-obsgyn.nl/>

The research nurse must explain to each subject the nature of this study, its purpose, procedures, expected duration and the potential risks and benefits involved in study participation along with any discomfort it may entail. Each subject must be informed that

participation in the study is voluntary and that withdrawal of consent will not affect his/her right to the most appropriate medical treatment or affect the doctor relationship.

This informed consent will be given by means of a standard written statement. It will be written so as to be easily understood by the subject. The subject will be given the time to read and understand the statement herself before signing her consent and dating the document. The subject will receive a copy of the written statement once signed.

The informed consent form must be considered as a part of the protocol with which it is to be submitted by the investigator to the IRB/Ethics committee.

Patients will be given a maximum of one week to consider their decision to participate in the study.

### **9.3 Objection by minors or incapacitated subjects (if applicable)**

Incapacitated adults will be not asked to participating in the study. Minors are excluded as well.

### **9.4 Benefits and risks assessment, group relatedness**

The ethical issues pertaining to this project will be discussed by considering the four ethical principles as discussed by Gillon. (37)

**Autonomy:** After the intake consultation and counseling session by the research nurse, the patient is given the choice to participate in the study. This process of informed consent respects her autonomy.

**Beneficence:** The advantages of a weight loss and exercise program in overweight or obese subfertile women (in order to improving chances of conception and eventually taking a baby home) have clearly been shown. Even if the patient does not conceive during the 6 months period, the health benefits of weight loss on the long-term are clearly in the interest of the patient.

**Non-maleficence:** In some reproductive medicine units, overweight or obese subfertile women are counselled and advised to loose weight before treatment is started. By starting this project, fertility treatment in the intervention arm will be delayed for a maximum of 6 months. There is no evidence that this short delay will influence the eventual pregnancy chances. The structured weight loss and exercise program will probably lead to higher spontaneous and therapy induced ongoing pregnancy chances. Patients with overweight or obesity have additional risks during pregnancy. The risks involve hypertension (OR 2.2), preeclampsia (OR 1.8-2.7) pregnancy diabetes (OR 2.2-3.4), cesarean section (OR 1.3-2.4) compared to normal weight women (see appendix table of evidence). These risks are not additionally influenced by fertility treatment. Lifestyle intervention aims to reduce the

involved pregnancy risks and is part of the analysis of this study. The lifestyle intervention *per se* does not involve additional risk to the patients, but reduces the risks of longterm health complications.

Before giving informed consent all eligible women are informed about the risks mentioned before (in writing in the patients' brochure). Women who are considered to be at the highest risk (i.e. those who have pre-existent hypertension or diabetes, or pregnancy induced hypertension, (pre)eclampsia or HELLP syndrome in a previous pregnancy) are excluded from participation. During the study adverse events will be monitored by a SMB.

Justice: Introducing the study will not infringe on other's rights (rights based justice). The study will mainly be financed through ZonMW and therefore no conflict distribution of scarce funds (distributive justice). Inclusion in the study respects all morally acceptable laws (legal justice).

